#### Moderators, baseline measures, and covariates

*Experiences in Close relationships-Revised Version, ECR-R* [70] is used to assess the caregivers’ own attachment style in terms of intimate, adult relationships. The ECR-R is the most frequently self-report measure of adult romantic attachment dimensions [73] and has been found highly reliable [74]. The scale consists of 36 items and measure attachment on two dimensions: (a) attachment avoidance (fear of intimacy and interpersonal dependence) and (b) attachment anxiety (fear of abandonment and a craving for interpersonal closeness). Avoidance and anxiety are continuous dimensions with attachment security defined as the absence of both. In some studies, the attachment avoidance and anxiety dimensions are highly correlated [73], and in this case, the ECR-R can be used as a one dimensional measure of attachment security by collapsing the two dimensions; security is then represented as low avoidance and anxiety, whereas insecurity is represented as high avoidance and anxiety [75]. ECR-R is part of an online survey that is distributed to both groups at T0.

*Structural factors*: Child–adult ratio is observed and noted by the observers who video-record the caregiver-child interactions in both groups at T0 and T2. Staff stability, child–adult ratio and grouping is assessed by online survey at T0 and T2 in both groups. Other factors regarding staff stability (e.g. sick leave, new hires, and use of substitutes) are measured via online surveys filled in by the managers of each childcare center at T0. Caregiver age, educational levels, and other background variables are measured by online survey filled in by the caregivers in both groups and at T0. The questionnaires used to measure structural factors were developed by The Danish Evaluation Institute (EVA) for other large scale evaluations of the quality of Danish childcare [76] and adapted by EVA for the purpose of this study.

#### Evaluation of feasibility and acceptability

To evaluate the feasibility of the intervention and how the participants experience the intervention in terms of its contribution to childcare practice, the following measures will be applied:

*The acceptability of intervention measure (AIM) *[71] is used to assess the caregivers’ and managers’ acceptability of the COS-C intervention. The AIM consists of four questions asking whether participants likes and welcomes the intervention and whether it meets their approval and is appealing to them.

*The feasibility of intervention measure (FIM) *[71] is used to measure whether the caregivers and their managers consider the COS-C intervention to be feasible to implement in a Danish early childcare context. The FIM consists of four questions asking whether the intervention seems implementable, possible, doable, and easy to use in practice.

The FIM and AIM are translated by the first and last author and piloted on a group of caregivers. AIM and FIM are distributed in both groups at T0 using an online survey, at T2 for the intervention group only, and at T4 for the waiting-list control group only.

*Client change interview (CCI)* [72, 77] will be used to assess how the participants experience the intervention, and is conducted individually with each caregiver and manager, who have participated in COS-C. The CCI will be conducted at T2 with the intervention group and at T4 with the waiting-list control group. The CCI is a semi-structured qualitative interview originally developed to help clients express their experience of therapy as freely as possible. The interview guide has been adapted to the childcare context for the purpose of this study. The caregivers are initially asked an open question where the they can speak freely about their experience of the intervention. Afterwards questions address changes experienced by the caregivers following the intervention, possible causes of these changes, aspects that were helpful and hindering and the experience of the research project. The interviews are audio recorded and verbatim transcribed using the software NVIVO.

### Sample size and power

The primary outcome for the study is the childcare providers’ sensitive responsiveness using the CIP-Scales [52]. Therefore, sample size was determined as the number of participants required to achieve min. 80% power for detecting a change in this measure with a two-sided alpha of 0.05. Two previous RCTs have examined interventions aiming at increasing professional caregivers’ sensitive responsiveness using the CIP-Scales. These studies find medium (*d* = 0.55) to large (*d* = 0.72) effects of the interventions on caregivers’ sensitive responsiveness post intervention. For normally distributed outcomes, a sample of 29 day care centers (15 intervention, 14 control corresponding to 110 caregivers) with each 3.4 caregivers yields a statistical power of 81% to detect an effect size of *d* = 0.55 using a two-sided alpha of 0.05, a correlation between baseline and post-intervention of 0.5 and an ICC of 0.1. This is the conservative estimate using the lowest effect size. If the effect size is 0.72 the statistical power rises to 96%.

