**Methods:**

A prospective, parallel, cluster-randomized wait-list controlled trial is used to test the efficacy of the attachment- and mentalization theory informed Circle of Security (COS) approach adapted to the childcare setting (COS-Classroom) on caregiver interactive skills and mind-mindedness. Participants are professional caregivers of children aged 0–2.9 years working in center-based childcare in Denmark. Approximately 31 childcare centers, corresponding to an estimated 113 caregivers, are expected to participate. The primary outcome is caregiver Sensitive responsiveness measured with the Caregiver Interactive Profile Scales (CIP-scales). Secondary outcomes include caregiver Mind-mindedness, the five remaining CIP-scales (Respect for autonomy, Structure and limit setting, Verbal communication, Developmental stimulation, and Fostering positive peer interactions), and caregivers’ resources to cope with work-related stress. Data on structural factors (e.g., staff stability, caregiver-child ratio, and level of pre-service education), caregiver attachment style, acceptability and feasibility of the COS-C together with qualitative data on how the participants experience the COS-C is additionally collected to investigate moderating and confounding effects.

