### Participants and procedure

Participants are caregivers from early childcare centers for children aged 0–2.9 years from Høje-Taastrup.

In February 2020, all managers of the early childcare centers (*N* = 35) in Høje-Taastrup were invited to participate in the project at a meeting held by the head of public childcare in the municipality and the Principal Investigator (PI, [name]). One of these childcare centers volunteered to participate in the pilot project. The remaining 34 center managers signed up for a visit in their center by the PI where their staff, i.e. the caregivers, were invited to participate. Due to the Covid-19 pandemic, some of these meetings were held online. At these meetings, the caregivers were informed about the project, it was made clear that participation was voluntary, and caregivers in each center were asked to consider whether they were interested in participating in the project. Subsequently, the managers gave their notice of participation to the project team.

While 28 of the initially invited childcare centers signed up for participation, six centers declined to participate. In 2021, two new childcare centers were established in the municipality; they were invited using the same procedure as described above and gave their consent for participation primo 2022. Currently, 30 childcare centers have consented to participate with a team, corresponding to approximately 110 caregivers, and all have been allocated to a time-period (see below for randomization procedures). Should more childcare centers (e.g., centers that are established after project start) be interested in participation, they will be informed about the project and enrolled accordingly. Figure 4 provides an overview of enrollment and allocation in the project. Data collection began in April 2021. Currently, participant enrollment and data collection is ongoing.

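### The sample-size statement contradicts itself: 29 centres of 3.4 caregivers is 98.6, not 110, so the text does not show which size the 81% power rests on

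*Protocol article*

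**What the plan says.** In the protocol article, Sample size and power, the sample is the "number of participants required to achieve min. 80% power for detecting a change in this measure", with a two-sided alpha of 0.05. The measure is Sensitive responsiveness on the CIP-scales. The sample is then given as "29 day care centers (15 intervention, 14 control corresponding to 110 caregivers) with each 3.4 caregivers", which "yields a statistical power of 81% to detect an effect size of" d = 0.55, assuming "a correlation between baseline and post-intervention of 0.5 and an ICC of 0.1". For d = 0.72 the stated power is 96%. The section names no test or reference distribution and mentions no loss of caregivers.

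Two other places give enrolment. Participants and procedure reports that "30 childcare centers have consented to participate with a team, corresponding to approximately 110 caregivers". The abstract's Methods paragraph says: "Approximately 31 childcare centers, corresponding to an estimated 113 caregivers, are expected to participate".

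**The concern.** One sentence gives three quantities of which any two fix the third, and they do not agree. This is the article's only power statement for the primary outcome, and the Strengths and limitations section cites the a priori power analysis as a merit of the study. A reader should be able to tell how many analysed caregivers the stated power needs. Here the answer could be about 99 or 110.

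The stated power is one point above the article's own minimum. At that margin, the choice of caregiver count and the allowance made for having only 29 clusters can decide whether the minimum is met.

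**Working it through.** **Inputs**, all from Sample size and power: 15 and 14 centres; 3.4 caregivers per centre or 110 in total; d = 0.55 and 0.72; two-sided alpha 0.05; baseline–post correlation r = 0.5; ICC = 0.1.

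**Step 1: the head count.**
- 29 × 3.4 = 98.6.
- If 3.4 is a rounded figure: 29 × 3.35 = 97.2 and 29 × 3.45 = 100.1, so about 97 to 100.
- 110 / 29 = 3.79 per centre.
- 110 / 3.4 = 32.4 centres.
- Gap: 110 − 98.6 = 11.4 caregivers, about 10% of 110.

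**Step 2: the power formula.** For m caregivers per centre and k1, k2 centres per arm, with baseline adjustment:

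SE = √[(1 − r²) × (1 + (m − 1) × ICC) × (1/(k1·m) + 1/(k2·m))], in SD units, with 1 − r² = 1 − 0.25 = 0.75.

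Power is taken at d/SE, either against the normal critical value of 1.96 or from a noncentral t with 29 − 2 = 27 degrees of freedom.

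**Step 3: m = 3.4.**
- Design effect: 1 + 2.4 × 0.1 = 1.24.
- SE = √[0.75 × 1.24 × (1/51 + 1/47.6)] = 0.194.
- d/SE = 2.83 for d = 0.55.

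**Step 4: m = 110/29 = 3.79.**
- Design effect: 1 + 2.79 × 0.1 = 1.28.
- SE = 0.187.
- d/SE = 2.94 for d = 0.55.

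| Size used | Reference distribution | Power, d = 0.55 | Power, d = 0.72 |
|---|---|---|---|
| Stated in the article | not named | 81% | 96% |
| 3.4 per centre (98.6) | normal | 80.8% | 95.9% |
| 3.4 per centre (98.6) | t, individual-level df | 80.0% | 95.6% |
| 3.4 per centre (98.6) | t, 27 df | 77.9% | 94.6% |
| 110 caregivers (3.79) | normal | 83.7% | 97.1% |
| 110 caregivers (3.79) | t, 27 df | 81.0% | 96.0% |

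Both stated powers are reproduced by the second row and by the last row. The printed result therefore cannot identify the size that was used.

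**Step 5: enrolment figures.** The same formula, with a t test on centres minus 2 degrees of freedom, no loss, and arms assumed to split as evenly as possible (d = 0.55):
- 30 centres and 110 caregivers (3.67 each, 15/15): 81.5%.
- 31 centres and 113 caregivers (3.65 each, 16/15): 82.6%.
- 31 centres at 3.4 each (16/15): 80.7%.

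**The case against.** The strongest reply is that the stated power is sound and only a caregiver count has slipped. Most of that stands.

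A reader might infer that the trial has 78% power and misses its own 80% minimum. The article does not support this. The 77.9% needs the smaller of the two printed sizes together with a 27-df t test, and the article names no test. At 3.4 per centre a normal approximation gives 80.8%, and a t test on individual-level degrees of freedom gives 80.0%. A centre-level test is a natural choice with 14 or 15 randomised centres per arm, but choosing it is commonly left to an analysis plan, which is not at hand.

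Nor can one say that these are the only two routes to 81% and 96%. Team sizes vary, according to Participants and procedure, and an allowance for unequal teams gives others. With 110 caregivers, a normal approximation and an assumed coefficient of variation of 0.5 in team size, power at d = 0.55 is also 81.0%.

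A reader might also take the reference to detecting a change as a planned change-score analysis, for which the stated power would be too high. The primary hypothesis compares levels after the intervention, and the stated power itself implies baseline adjustment. The phrase reads as ordinary wording.

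Finally, enrolment runs at about 3.65 to 3.67 caregivers per centre, and power there is above 80% even with the stricter test. That limits the consequence. It does not remove the contradiction in the sentence.

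**Conclusion.** The point holds as an internal inconsistency of minor severity. The per-centre size and the total differ by about 11 caregivers (10%), which neither rounding nor any stated dropout allowance explains. The stated 81% and 96% are not shown to be wrong, since each printed size reproduces both under a reasonable method. What is missing is which size and which reference distribution produced them.

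The conditional result is worth stating: if 3.4 is right and a centre-level t test is used, power for d = 0.55 is about 78%, roughly two points under the minimum. At the reported or expected enrolment the same test gives 81.5% to 82.6%, assuming no loss and near-equal arms.

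All these figures rest on the article's d, ICC and correlation. Apart from the unequal-team-size example, they also assume equal team sizes. All use the baseline-adjusted variance factor of 0.75, which the article does not write out but which its stated power implies.

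**What to change.** Restate the sentence as one consistent set: centres, analysed caregivers per centre, total, reference distribution and resulting power. Two versions are consistent:

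- Change 3.4 to 3.8 per centre (29 × 3.8 = 110.2), keep 110 and 81%, and state that the power comes from a t test on 27 centre-level degrees of freedom.
- Keep 3.4, change 110 to about 99, and report 81% by normal approximation together with about 78% by a centre-level t test.

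If 3.4 is the number expected to remain after attrition, say so and give the assumed loss.

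The cost is wording only. Under the second version a slightly less favourable figure would appear beside the present one. No participants, centres or design features change.

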## Discussion

It is well-documented that the quality of the interactions that children have with their professional caregives impacts their development across various important domains well beyond the first years of life [5, 10, 11]. Particularly children from at-risk backgrounds are found to benefit from high quality childcare in various developmental domains [9, 18–20]. Therefore, caregivers’ ability to understand and respond to the children’s needs, also when children do not communicate their needs clearly is pivotal. This study protocol presents the first RCT testing the efficacy and feasibility of the COS-C, an attachment- and mentalization-based intervention originally developed as a parenting program but adapted to the childcare context. The setting is Danish center-based childcare with children aged 0–2 year.

Overall, it is hypothesized that the intervention will enhance caregivers’ sensitive responsiveness and mind-mindedness as well as other dimensions of caregiver interactive skills. Although a previous quasi-experimental study has shown promising results in terms of supporting childcare providers’ self-efficacy and empathy using the Circle of Security approach [54], it has not been examined whether these effects translate into professional caregivers’ sensitive behavior and mind-mindedness towards the children in their care.

### Strengths and limitations

The most important strength of the study is the randomized controlled design. While previous quasi-experimental studies have shown promising results in terms of using the Circle of Security-approach for professional development [54], no previous studies have examined this in a randomized controlled trial. Furthermore, in a meta-analysis on the effects of interventions in childcare, the authors concluded that although interventions targeting caregiver-child interactions are moderately effective, we need more studies with sufficient power and high-quality measures [24]. This study contributes to the literature in both of these respects:

First, we conducted an a priori power analysis to determine sample size in the present study, and compared to the studies in the aforementioned meta-analysis, this study is among the largest studies examining the effects of interventions targeting childcare providers’ interactive skills. Second, we use well-validated, reliable and theoretically sound measures for capturing changes in childcare providers’ interactive skills [52] and mind-mindedness [42]. In particular, the use of an observational measure for capturing childcare providers’ interactive skills during naturalistic situations is an important merit of the present study. Furthermore, the use of observational measures rated by blinded coders reduces the bias associated with self-report.

Third, apart from evaluating the effectiveness of the COS-C, the present study also aims at examining the mechanisms of change. In a mediation analysis, we will examine whether the COS-C improves caregiver’s interactive skills through supporting their mentalizing abilities, here operationalized as caregiver mind-mindedness. This knowledge will contribute to the development of interventions targeting childcare providers’ interactive skills, and since few studies have examined the links between mentalizing and interactive skills in professional caregivers [47], the knowledge will also contribute to our theoretical understanding of factors underlying professional caregivers’ sensitive and insensitive responses to children in their care.

Fourth, the mechanisms of change and the implementation of the COS-C are examined using a mixed-methods approach. Acceptability and feasibility is measured using validated measures [71] and the questionnaires are combined with an adapted version of the qualitative semi-structured Client Change Interview (CCI), which has been used extensively to study client’s experience of therapy-processes [72]. The qualitative approach provides in-depth information about mechanisms of change and implementation of the COS-C in a Danish center-based childcare setting, and allows for hypothesis generation. We believe that the combined qualitative and quantitative results will contribute to the development of interventions for childcare providers in general, and further adaptation of the COS-C to the childcare setting. Also, a focus on implementation is a considerable strength because research-based interventions might not be effective in real-life practices when implementation is unsuccessful [62].

Fifth, it is a strength that the study is conducted in a municipality where the proportion of at-risk and low-SES families is relatively high compared to other Danish municipalities. However, this strength also implies some limitations as the specific characteristic of this study sample limits generalization of results to populations with a different SES background. Yet, given the findings of reviewed literature herein, it is important to investigate the effects of the COS-C in a more at-risk population where the children are particularly vulnerable for developing insecure attachments with their professional caregivers with subsequent consequences for long-term developement [33].

Finally, randomization is conducted at the center level, ensuring that teams in the intervention group and waiting-list control group come from different childcare centers, thereby preventing a potential “spillover” effect from the intervention group to the control group.

The study also has some limitations. First, as the caregivers all work within the same municipality, there is a risk of information flow about the intervention principles from the intervention group to the waiting-list control group. However, the randomization process is designed to reduce such biases by ensuring that allocation to the intervention is conducted at the center level.

Second, considerations should also be made in relation to the choice of a waiting-list control group because effect size estimates have been found to vary depending on the control condition, and waiting-list control groups generates larger effect sizes than no treatment or psychological placebo in psychotherapy research [78]. Whether this applies for interventions tested in the childcare context is unknown. The waiting-list design also makes it impossible to collect follow-up data to examine long-term effects. Nevertheless, if this trial shows an effect of COS-C, future studies would benefit from comparing COS-C to other interventions targeting caregiver-child interaction in childcare or modified interventions of the COS-C, e.g. COS-C with added video feedback. These studies would shed light on what components are most effective in supporting childcare providers’ interactive skills.

Finally, and most importantly, we do not measure effects of the intervention on child outcomes. Thus, in the case that the intervention improves childcare providers’ interactive skills and/or mind-mindedness, we will not know the extent to which these effects translate into positive child outcomes. Meta-analytic evidence shows that previous interventions targeting caregiver-child interactions in childcare show moderate effects on outcomes related to childcare providers and only small effects on child outcomes [24]. An evaluation of the effects of COS-C on child well-being and developmental outcomes would require a different design, a larger sample, and importantly, more extensive data collection. Before conducting such a resource-extensive study, we believe that it is important to establish the effect of COS-C on caregiver outcomes. Moreover, as child outcomes and caregiver-child attachment quality is directly linked with caregiver interactive skills [11, 33], we consider testing effects on caregiver MM and sensitivity a first important step. If COS-C shows an effect at the caregiver level, future studies should examine the effect of COS-C on caregiver-child attachment quality and child outcomes.

In conclusion, the presented RCT will evaluate the effect, mechanisms of change, and implementation of COS-C, an attachment-based group intervention aiming at promoting caregiver-child sensitivity and Mind-Mindedness in a Danish early childcare setting. The results of the study will provide insight on if offering a systematic manualized short-term intervention can improve the quality of care offered in Danish childcare centers, potentially informing policy makers on how to ensure high-quality childcare, which is of great importance for children’s current and long-term wellbeing and development.

